### Outcome measures

The primary outcome measure is the *Quick-*DASH (Disabilities of the Arm, Shoulder and Hand) score, which reflects both function and pain [15]. The DASH Outcome Measure is a validated 30-item, self-reported questionnaire designed to help describe the disability experienced by people with upper-limb disorders and also to monitor changes in symptoms and function over time [15,16].

The *Quick-*DASH is a shortened version of the DASH Outcome Measure. Instead of 30 items, the Quick-DASH uses 11 items (scored 1-5) to measure physical function and symptoms in people with any or multiple musculoskeletal disorders of the upper limb. The right and left elbow will be assessed separately. At least 10 of the 11 items must be completed for a score to be calculated. The scores will be transformed to a 0-100 scale for easy comparison. A higher score indicates greater disability.

Like the DASH, the *Quick-*DASH contains 2 optional modules to measure symptoms and function in athletes, performing artists and other workers whose jobs require a high degree of physical performance. These optional models are scored separately; each contains four items, scored 1-5. All items must be completed for a score to be calculated.

The secondary outcome measures are:

• Functional outcome (Mayo Elbow Performance Index and Oxford Elbow Score)

• Pain level at both sides (VAS)

• Range of Motion of the elbow joint at both sides

• Rate of secondary interventions

• Rate of complications (secondary dislocation, instability, relaxation)

• Health-related quality of life: SF-36 and EQ-5D

• Radiographic appearance of elbow joint (degenerative changes and heterotopic ossifications)

• Cost

• Cost-effectiveness

The MEPI index is one of the most commonly used physician-based elbow rating systems. This index consists of five parts: pain (with a maximum score of 45 points), ulnohumeral motion (20 points), stability (ten points), the ability to perform five functional tasks (5 × 5 points) and the patient response. If the total score is between 90 and 100 points, it is considered excellent; between 75 and 89 points, good; between 60 and 74 points, fair; and less than 60 points, poor [17].

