### Sample size calculation

Calculation of the required sample size is based upon the assumption that the mean *Quick-*DASH will be 12.5 in plaster treated patients and five in the functional group, assuming a standard deviation of 15 for the plaster group and 7.5 for the functional group [7]. A 2-sided test with an α level of 0.05 and a β level of 0.2 requires 41 patients in each group. Anticipating a dropout rate of 20% loss to follow-up a sample size of 50 patients in each arm is required.

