### Statistical analysis

Data will be analyzed using the PASW Statistics version 18.0.1 or higher (SPSS, Chicago, Illinois, USA). Normality of continuous data will be tested with the Shapiro-Wilk and Kolmogorov-Smirnov test and by inspecting the frequency distributions (histograms). The homogeneity of variances will be tested using the Levene's test.

The analysis will be performed on an intention to treat basis. Patients with protocol violations will be followed up, and data will be recorded. Data will be analyzed with and without inclusion of patients with protocol violation.

Descriptive analysis will be performed to report baseline characteristics (intrinsic variables and injury-related variables) in both treatment groups. For continuous data (e.g., age, Quick-DASH score at baseline) mean ± SD (parametric data) or medians and percentiles (non-parametric data) will be calculated. For categorical data (e.g., gender, ASA grade, alcohol and tobacco consumption, dominant and affected side) frequencies will be calculated.

The mean difference between the mean *Quick-*DASH scores of the functional group and the plaster group will be tested. Univariate analysis will be performed to test the difference in the primary and secondary outcome measures between the functional and the plaster groups. Continuous data will be tested using a Student's T-test (parametric data) or a Mann Whitney *U*-test (non-parametric data). Chi-square analysis will be used for statistical testing of categorical data. A p-value <0.05 will be taken as the threshold of statistical significance.

A multivariable linear regression analysis will be performed to model the relationship between different covariates and the *Quick-*DASH score. Intrinsic and injury-related variables that display a p-value <0.5 in the univariate analyses will be added as a covariate.

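### The plan states and sizes a difference in mean Quick-DASH, but its normality rule will almost certainly make the primary test a Mann-Whitney test, which does not address that difference

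*Protocol article*

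**What the plan says.** All references are to the protocol article.

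- **Stated contrast (Statistical analysis).** The sentence opens with "The mean difference between the mean" and goes on to say that the Quick-DASH "scores of the functional group and the plaster group will be tested". This is a comparison of means.
- **Choice of test (same paragraph).** For primary and secondary outcomes alike, continuous data go to a Student's "T-test (parametric data) or a Mann Whitney *U*-test (non-parametric data"). The section's first paragraph plans Shapiro-Wilk, Kolmogorov-Smirnov and histogram checks of normality. It also plans Levene's test, but nothing is said to follow from its result.
- **Sizing (Sample size calculation).** The planning means are 12.5 (plaster) and 5 (functional). For the spread, the calculation proceeds by "assuming a standard deviation of 15 for the plaster group and 7.5 for the functional group". With two-sided α of 0.05 and power of 0.80, it arrives at 41 per group.
- **Scale (Outcome measures).** "The scores will be transformed to a 0-100 scale for easy comparison".

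**The concern.** Student's t compares means. Mann-Whitney asks whether scores in one arm tend to exceed scores in the other. The two questions coincide only under extra conditions, such as arms that differ by a shift alone. The planning figures exclude a pure shift, because they give one arm twice the SD of the other.

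A rule that picks the test from the data therefore also picks the hypothesis. If the planning figures already determine that the rule leads to the rank test, the trial would report a p-value for a question that it neither stated nor powered. That p-value could also conflict with the mean difference printed beside it.

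**Working it through.** **Step 1. Reproduce the sample size.** Difference 12.5 − 5 = 7.5. Root-mean-square SD = √((15² + 7.5²)/2) = 11.86. The normal approximation gives n = 2 × (11.86 × (1.96 + 0.84)/7.5)² ≈ 39.2, so 40 per group. With the noncentral t distribution, Student's t has power 0.798 at 40 and 0.808 at 41. The stated 41 is reproduced, as the size for a comparison of means.

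**Step 2. Can the scores be normal under the plan's own figures?** A normal curve with these moments would put Φ(−12.5/15) = 20% of plaster scores and Φ(−5/7.5) = 25% of functional scores below zero, where the scale ends. So no: the distributions must be clearly right-skewed or piled up near zero.

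**Step 3. Which branch does the rule take?** The document gives means and SDs but no shape, so shapes are an assumption and a range is shown. Trials of 41 per arm were simulated under the planned means and SDs, with scores rounded to the 44 steps that 11 items scored 1-5 allow. Shapiro-Wilk rejected normality in at least 99.9% of samples in each arm, for all four shapes below.

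**Step 4. Power at the planned effect (41 per arm, 10,000 trials per shape).**

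| Assumed shape | Mann-Whitney | Welch |
|---|---|---|
| Normal censored at zero | 0.60 | 0.84 |
| Beta | 0.79 | 0.85 |
| Gamma | 0.89 | 0.87 |
| Lognormal (capped at 100; realised SDs 13.6 and 7.2) | 0.99 | 0.91 |

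A gamma with extra zeros (35% in plaster, 45% in functional) gives about 0.65 against 0.84. At the planned effect, Mann-Whitney and Welch reached opposite significance verdicts in about 10% to 11% of trials (gamma) and 21% (gamma with extra zeros).

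**Step 5. Equal means, different spreads.** Both arms were given the same mean (8.75 or 12.5), with target SDs of 15 and 7.5. Mann-Whitney was significant in 27% to 69% of trials across the four shapes, and Welch in 5% to 7%. This shows that the rank test does not test the mean difference. It is not an error rate under no treatment effect.

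**Step 6. No effect at all.** With both arms drawn from one gamma distribution (mean 12.5, SD 15, or mean 5, SD 7.5), Mann-Whitney rejected in about 5% of trials.

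**Step 7. The t branch.** The assumed variance ratio is 15²/7.5² = 4. The size of Student's t on normal data with these SDs (50,000 trials) was:

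| Plaster / functional evaluable | Student's t | Welch |
|---|---|---|
| 41 / 41 | 5.0% | 4.9% |
| 37 / 45 | 6.6% | 5.0% |
| 45 / 37 | 3.9% | 5.1% |
| 33 / 50 | 8.6% | 5.1% |
| 50 / 33 | 2.9% | 5.2% |

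**The case against.** The best defence is that a rank test is a legitimate choice for a skewed, bounded score. It is a valid test of no difference in distribution, it holds its level when treatment does nothing, and for some shapes it is the more powerful test. All of this stands. A power shortfall is possible but not established: of the four main shapes, two exceed 80%, one is a point short and one is well below.

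Three stronger readings are tempting, and the document does not support them.

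- **That the false-positive rate is 27% to 69%.** Those figures come from arms with equal means but different spreads, so treatment has changed the distribution. Almost every significant result there favoured plaster, so they do not point to false claims for functional treatment.
- **That the plan contradicts itself by rejecting equal variances and then assuming them.** It rejects nothing. It sizes on unequal SDs and schedules Levene's test. What follows from that test is a detail that a condensed article may leave to the full protocol or SAP.
- **That Student's t is seriously mis-sized.** With near-equal arms it is not. The worst figures need a marked imbalance: 33 of 50 in one arm is 34% loss, against none in the other. The document anticipates 20% loss and no difference between arms. The branch would also seldom be reached.

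It could also be argued that the planned linear regression supplies a mean comparison. It is described as modelling how covariates relate to the score, and it is not named as the primary test.

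None of this removes the mismatch, which lies in text that is present: one paragraph states a mean difference and then gives a rule that leads elsewhere.

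**Conclusion.** The point holds. On the plan's own means, SDs and scale, the stated rule sends the primary analysis to Mann-Whitney in practically every trial, while the stated contrast and the sample size concern means. That the data are non-normal follows from the planning figures and the bounded scale. The power range (about 60% to 99%, against 84% to 91% for Welch) and the disagreement rate (about 10% to 21%) depend on the assumed shapes. They show that the planned 80% is not assured for the test that would be run, not that it is missed.

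The wording on unequal variances is a minor point. The t branch names only Student's t, although the sizing assumes a 4:1 variance ratio. This matters only if dropout unbalances the arms markedly.

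**What to change.** Prespecify one primary analysis: the difference in mean Quick-DASH between arms with its 95% CI, by a method that allows unequal variances (Welch, or a linear model with robust or bootstrap standard errors). State that it applies whatever the normality and Levene tests show. Keep Mann-Whitney as a sensitivity analysis. Settle this before anyone sees outcomes by arm, because a later choice could look driven by the results.

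The cost is wording only. Welch's normal-theory power is 0.804 at 41 per group (0.794 at 40), so no extra patients are needed. The downside is that a rank test would be more powerful for some skewed shapes, for example 0.99 against 0.91 in the lognormal case.

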## Abstract

**Background:**

Elbow dislocations can be classified as simple or complex. Simple dislocations are characterized by the absence of fractures, while complex dislocations are associated with fractures. After reduction of a simple dislocation, treatment options include immobilization in a static plaster for different periods of time or so-called functional treatment. Functional treatment is characterized by early active motion within the limits of pain with or without the use of a sling or hinged brace. Theoretically, functional treatment should prevent stiffness without introducing increased joint instability. The primary aim of this randomized controlled trial is to compare early functional treatment versus plaster immobilization following simple dislocations of the elbow.

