Three observational studies comparing different periods of plaster immobilization after reduction showed a larger ROM after shorter immobilization, but this finding was statistically significant in only one study [9-11]. Moreover, these studies may be confounded by the severity of the injury, as worse cases were probably immobilized longer.

An important question following reduction of simple elbow dislocations is whether or not the elbow is stable. Signs of instability are redislocation, a positive pivot shift test, positive valgus and varus stress testing, and radiographic incongruence. In the studies described above, stability testing was either not performed, or the tests differed between the studies. In these eight studies, only one recurrent dislocation after plaster treatment was mentioned [7] (i.e., one recurrence in 342 patients (0.3%)), and signs of gross instability were not mentioned. Therefore, we conclude that the majority of the patients included in these studies had simple dislocations, which remained stable after reduction. For this type of dislocation, literature suggests that plaster immobilization for more than two weeks following reduction may lead to limited ROM [12,13]. Therefore some authors state that early functional treatment should be the treatment of choice. Functional treatment is defined as early active movements within the limits of pain with or without the use of a sling or a hinged brace [6-8].

A recent electronic survey of 90 trauma surgeons in the Netherlands revealed that 60% of the patients with a simple elbow dislocation were generally treated with plaster immobilization for three weeks or longer [14].

The primary objective of this study is to compare the *Quick-*DASH (Disabilities of the Arm, Shoulder, and Hand) questionnaire scores after functional treatment versus plaster immobilization in adult patients who sustained a simple elbow dislocation. Secondary aims are to examine the effect of functional treatment versus plaster immobilization on functional outcome (Mayo Elbow Performance Index (MEPI) and Oxford elbow score), the level of pain (Visual Analog Scale (VAS)), ROM, the rate of secondary interventions and complications, health-related quality of life (Short Form-36 (SF-36) and EuroQol-5D (EQ-5D)), costs, and cost-effectiveness in these patients.

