The Oxford elbow score is a 12-item questionnaire. It is comprised of three one-dimensional domains: elbow function, pain and social-psychological, with each domain comprising 4 items with good measurement properties [18]. This is a validated questionnaire in the UK and was translated to Dutch by the proper translation procedure, which uses the technique of translation and back-translation [19]. Permission for translation and the use of the OES for this study was obtained from Oxford and Isis Outcomes, part of Isis Innovation Limited (website: http://www.isis-innovation.com/)

Pain level will be determined using a 10-point Visual Analog Scale (VAS), in which zero implies no pain and ten implies the worst possible pain.

ROM will be measured on both sides using a goniometer.

Secondary interventions within one year of initial treatment to relieve pain or improve function will be recorded. This includes secondary revision of collateral ligaments and external fixator placement.

Complications within one year of initial treatment will be recorded. These include redislocation, pressure necrosis (plaster group only), post-traumatic dystrophy, and neurologic deficit.

The Short-Form 36 (SF-36) is a validated multi-purpose, short-form health survey with 36 questions that represent eight health domains that are combined into a physical and a mental component scale [20]. The Physical Component Scale (PCS) combines the health domains of physical functioning (PF; ten items), role limitations due to physical health (RP; four items), bodily pain (BP; two items), and general health perceptions (GH; five items). The Mental Component Scale (MCS) combines the health domains of vitality, energy, or fatigue (VT; four items), social functioning (SF; two items), role limitations due to emotional problems (RE; three items), and general mental health (MH; five items). Scores ranging from zero to 100 points are derived for each domain, with lower scores indicating poorer function. These scores will be converted to a norm-based score and compared with the norms for the general population of the United States (1998), in which each scale was scored to have the same average (50 points) and the same standard deviation (ten points).

The EuroQol-5D is a validated questionnaire for health-related quality of life [21,22].

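### Chi-square at p<0.05 is the only stated comparison for complications, yet at the article's own redislocation rate it would be incomputable or uninformative; an interval for the risk difference is needed

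*Protocol article*

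**What the plan says.** The Outcome measures section of the protocol article lists "Rate of complications (secondary dislocation, instability, relaxation") and the rate of secondary interventions among the secondary outcomes. It adds that "Complications within one year of initial treatment will be recorded", and of these complications it says: "These include redislocation, pressure necrosis (plaster group only), post-traumatic dystrophy, and neurologic deficit".

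The Statistical analysis section states: "Univariate analysis will be performed to test the difference in the primary and secondary outcome measures between the functional and the plaster groups". For the categorical outcomes the rule is "Chi-square analysis will be used for statistical testing of categorical data", and "A p-value <0.05 will be taken as the threshold of statistical significance". Continuous outcomes have a fallback, the Mann-Whitney test when data are not normal. Categorical outcomes have no alternative for small counts, and no risk difference or interval is named for harms.

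Two other places bear on the point. The Background of the abstract gives the rationale that, in theory, "functional treatment should prevent stiffness without introducing increased joint instability". The main Background pools eight earlier studies and reports a single recurrent dislocation, after plaster: "one recurrence in 342 patients (0.3"%).

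**The concern.** The expected benefit of early motion is less stiffness, and the natural counterweight is instability or redislocation. The trial therefore needs to say something useful about those events. A chi-square p-value is a poor vehicle when almost no events are expected. If neither arm has an event, the statistic does not exist. If there are one or two events, the p-value cannot reach 0.05 and shows nothing about how large an excess remains possible.

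At stake is what the trial can conclude on harm. The primary Quick-DASH comparison is not affected.

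**Working it through.** **Inputs.** Redislocation: 1 in 342 (Background). Patients: 50 per arm, with 20% loss anticipated, so 50 × 0.8 = 40 followed (Sample size calculation). Test: chi-square, p<0.05 (Statistical analysis). Applying 1/342 to both arms is an assumption.

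**The article's own figure.** 1/342 = 0.0029 = 0.29%, which agrees with the printed 0.3%.

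**Expected events.**
- Per arm: 50 × 1/342 = 0.146.
- Whole trial: 100/342 = 0.29.
- Chance of none in the trial: (1 − 1/342)^100 = 0.746. Every expected event count is then zero and the chi-square statistic is 0/0.

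**Uncertainty in the base rate.** The exact 95% interval for 1/342 is 0.007% to 1.6%. Multiplied by 50, this is 0.004 to 0.8 events, so fewer than one redislocation per arm is expected across the whole interval.

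**What zero events would leave open.** The two-sided exact 95% upper limit for 0/n is 1 − 0.025^(1/n).
- n = 50: 7.1%, about 24 times 0.29%.
- n = 40: 8.8%, about 30 times 0.29%.

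For the risk difference with zero events in both arms of 50, the Newcombe limits are ±1.96²/(50 + 1.96²) = ±3.84/53.84 = ±7.1 percentage points.

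**Power at 50 per arm.** By exact binomial enumeration, two-sided 0.05, plaster rate 0.29%:

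| True rate, functional arm | Chi-square, uncorrected | Fisher's exact |
|---|---|---|
| 2.9% (tenfold) | 5% | 0.3% |
| 5% | 21% | 3% |
| 10% | 68% | 35% |
| 15% | 91% | 74% |

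**Type I error of uncorrected chi-square at 50 per arm**, same enumeration, equal rates in both arms: 0.00003 at 1/342, 0.002 at 1%, 0.013 at 2%, 0.043 at 5%. The test is conservative at these rates.

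**Dependence on the version of the test, 50 per arm.**

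| Split | Uncorrected | Continuity-corrected | Fisher |
|---|---|---|---|
| 2 vs 0 | 0.153 | 0.475 | 0.495 |
| 4 vs 0 | 0.041 | 0.126 | 0.118 |
| 5 vs 0 | 0.022 | 0.067 | 0.056 |
| 6 vs 0 | 0.012 | 0.035 | 0.027 |

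The article does not say which version of chi-square is meant. With 4 or 5 events against none, that choice decides significance.

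**The case against.** The best case for the plan has four parts.

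1. *An article condenses.* A small-cell fallback and interval estimates may stand in a full analysis plan that is not shown. This limits the point. The article's silence on intervals is not proof that none is planned, and defining the outcomes as rates implies that per-arm rates will be shown. But the article does state a test and a threshold for categorical data, and that stated rule does not suit redislocation.

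2. *No trial of 100 patients can be powered for a 0.3% event.* This is true, and the point asks for neither more patients nor a non-inferiority margin. It asks for a summary that shows the uncertainty.

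3. *The test is not useless.* This also stands. A very large excess would probably be found: 91% power for 15% against 0.3%. A reader might infer that a non-significant result is nearly certain whatever the harm; the power figures contradict that for large excesses. A reader might also infer from the 4 vs 0 split that uncorrected chi-square gives too many false positives. The type I error figures contradict that at these rates. The split shows only that the test versions disagree and that Fisher's test is the stricter.

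4. *The base rate is narrow.* It concerns redislocation only, comes from studies of mixed treatments, and rests on one event after plaster. The argument cannot be carried over numerically to instability, dystrophy, neurologic deficit or secondary interventions.

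A further tempting reading is that the trial intends to report non-significance as equal safety. Nothing in the article says so. The remark on instability is background rationale, not a safety hypothesis.

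**Conclusion.** The point holds for redislocation. At the article's own rate the planned comparison would most likely have no events to compare (75%). With one or two events, all in one arm, it could not reach significance. Meanwhile 0/50 leaves true rates up to 7.1% open, and 0/40 up to 8.8%. Power for a moderate excess, 5% against 0.3%, is about 21%.

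This rests on carrying 1/342 to both arms, on the stated 50 per arm, and on reading chi-square as uncorrected. The first assumption matters little, because the whole exact interval for the base rate gives fewer than one expected event per arm. For the other complications and for secondary interventions the article gives no rate. The same reporting is sensible there, but the size of the problem is unknown.

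This is a weakness in a secondary analysis that is worth correcting because the correction is nearly free and changes what can be said about harm.

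**What to change.** In the Statistical analysis section, add for each complication type and for secondary interventions:

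- the number of patients with the event in each arm;
- the risk difference with a 95% confidence interval suited to small counts (exact or Newcombe);
- a statement that the safety conclusion will rest on the upper limit of that interval, meaning the largest excess not excluded, and not on a non-significant p-value.

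If a p-value is also given where expected counts are below 5, name a small-sample test in advance. Fisher's exact test is the usual choice but has a price: for 5% against 0.3% its power is 3%, compared with 21% for uncorrected chi-square. The interval should therefore carry the conclusion.

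The cost is two or three sentences and slightly more analysis, with no extra patients, visits or data. The safety statement will be less favourable than a bare non-significant result.

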Radiographic appearance (anteroposterior and lateral X-ray at one year): heterotopic ossification will be classified according the classification scheme of Broberg and Morrey as a bone exostosis or as a soft tissue ossification of a ligament, capsule or muscle ("myositis ossificans") [23]; degenerative changes will be classified as grade zero (no change), grade 1 (slight narrowing of the joint space with small osteophytes), grade 2 (moderate narrowing of the joint space, osteophytes and subchondral sclerosis), and grade 3 (severe narrowing of the joint space, large osteophytes, subchondral sclerosis and cystic deformation).

The incremental cost-effectiveness ratio of functional versus plaster treatment will be expressed in a cost-utility ratio, i.e., in terms of cost per QALY. The economic evaluation will be performed from a societal perspective, and will include both health care costs and costs of production losses. Health care costs will include costs of general practice care, medical specialist care, physical therapy, hospitalization, medication, and other costs directly associated with diagnosis, treatment and rehabilitation. Patients will be asked to administer a custom-made questionnaire to register their health care needs and production loss.

In addition to the outcome variables mentioned above, the following data will be collected:

a) Intrinsic variables (baseline data): age, gender, American Society of Anesthesiologists' ASA classification, tobacco consumption, alcohol consumption, comorbidity, social status/household composition, dominant side, and medication use.

b) Injury related variables: affected side, mechanism of injury, and assessment of varus, valgus and posterolateral rotatory instability.

c) Intervention-related variables: reduction delay (i.e., time between dislocation and reduction), time between injury and start of physical therapy, days of sling use, and number of physical therapy sessions

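### The only test named for categorical outcomes is chi-square, which ignores the order of the degenerative grades 0 to 3 and loses power if treatment shifts them consistently in one direction

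*Protocol article*

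**What the plan says.** The Statistical analysis section applies univariate tests to the primary and secondary outcomes and chooses the test by data type. For measurements: "Continuous data will be tested using a Student's T-test (parametric data) or a Mann Whitney *U*-test (non-parametric data"). For everything else: "Chi-square analysis will be used for statistical testing of categorical data". It makes no distinction between ordered and unordered categories.

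The Outcome measures section lists among the secondary outcomes "Radiographic appearance of elbow joint (degenerative changes and heterotopic ossifications"). The two components are scaled differently:

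- Degenerative change is an ordered severity scale: "degenerative changes will be classified as grade zero (no change), grade 1" and so on up to grade 3, with narrowing that goes from slight through moderate to severe.
- Heterotopic ossification is recorded by type, "as a bone exostosis or as a soft tissue ossification of a ligament, capsule or muscle", and these types have no order.

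The degenerative grade is not named in the Statistical analysis section. That section does treat another ordered scale, ASA grade, as categorical when it describes the baseline summaries: "For categorical data (e.g., gender, ASA grade, alcohol and tobacco consumption, dominant and affected side) frequencies will be calculated".

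**The concern.** A Pearson chi-square on a 2 by 4 table asks whether the two arms differ in any way at all. Relabel the grades in any order and the p-value does not change. The clinical question for a severity grade is narrower: does one treatment lead to worse grades than the other? An ordered test puts that question to one degree of freedom, whereas chi-square spreads it over as many as three.

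The trial was not sized for this outcome. A real shift in degenerative change could therefore more easily come out as non-significant under a test that sets aside part of the information recorded. The plan already contains a suitable test: Mann-Whitney handles ordered grades with ties, but the article reserves it for continuous data.

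**Working it through.** **1. The plan's own figure.** The Sample size calculation section gives 41 evaluable patients per group for the Quick-DASH (means 12.5 and 5, SDs 15 and 7.5, two-sided α 0.05, power 0.80):

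n = (1.960 + 0.842)² × (15² + 7.5²) / 7.5² = 7.849 × 281.25 / 56.25 = 39.2, so 40 by the normal approximation.

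The t-based solution is 40.2, so 41, and Welch power at 41 is 0.804. The figure reproduces. I use 41 per arm below as the assumed number with a one-year radiograph. The article states no power for that outcome.

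**2. Loss from extra degrees of freedom alone.** Fix the noncentrality that gives a 1-df test the stated power, and apply the same noncentrality to a 3-df test (α 0.05):

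| 1-df power | Noncentrality | 3-df power | Difference (points) |
|---|---|---|---|
| 0.20 | 1.242 | 0.133 | 6.7 |
| 0.50 | 3.841 | 0.345 | 15.5 |
| 0.60 | 4.899 | 0.432 | 16.8 |
| 0.70 | 6.172 | 0.531 | 16.9 |
| 0.80 | 7.849 | 0.645 | 15.5 |
| 0.90 | 10.507 | 0.784 | 11.6 |

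The loss is largest at moderate power and shrinks at both ends.

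**3. Simulation with assumed grades.** The plaster distributions and the effect sizes are my assumptions; the article gives neither. The functional arm follows from a proportional-odds shift, in which each cumulative odds is multiplied by the odds ratio (OR). For plaster 50/30/15/5% and OR 2.5, the cumulative odds 1, 4 and 19 become 2.5, 10 and 47.5, so the functional arm is 71.4/19.5/7.0/2.1%. Pearson chi-square on the non-empty grades is compared with the tie-corrected Mann-Whitney, 41 per arm:

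| Plaster grades 0/1/2/3 (%) | OR | Chi-square power (%) | Mann-Whitney power (%) | Gain (points) |
|---|---|---|---|---|
| 50/30/15/5 | 2.5 | 37 | 54 | 17 |
| 50/30/15/5 | 3.5 | 59 | 77 | 18 |
| 60/28/10/2 | 2.5 | 32 | 48 | 16 |
| 60/28/10/2 | 3.5 | 52 | 69 | 17 |
| 75/18/5/2 | 2.5 | 18 | 34 | 16 |
| 75/18/5/2 | 3.5 | 32 | 52 | 20 |

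These rows rest on 6,000 tables each. Larger independent runs agree to within about 2 points.

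**4. How far the gain moves with the assumptions.**

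- Small shift, OR 1.5: 9.7% against 15.8% at 50/30/15/5%, a gain of 6 points. It is about 5 to 6 points over the three distributions above.
- Very large shift, OR 6, at 50/30/15/5%: 86.9% against 95.4%, a gain of 9 points, because both tests are near their ceiling.
- Grades 85/12/2/1%: gain of 4 points (OR 1.5) to 20 points (OR 6).
- About 95% in grade 0: gain of about 2 points at OR 1.5 and 3 to 6 from OR 2 to OR 6.
- A non-monotone difference reverses the sign: in one example chi-square has 69% power and the rank test 6%.

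**5. Size and degrees of freedom.** With no effect, over the three distributions in step 3, chi-square rejects in about 3 to 5% of tables and Mann-Whitney in about 5%. Both are valid, with chi-square on the conservative side. Empty grades drop out of the table, so chi-square often has fewer than 3 df: on average 2.0 to 2.4 at 85/12/2/1% and 1.3 to 1.6 when about 95% are grade 0.

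**The case against.** The strongest objection is that this is one generic sentence in a condensed article, that the test for one ordinal component of a secondary outcome is usually left to the analysis plan, and that the sentence does not name the degenerative grade. That limits the weight of the point but does not remove it. The article does state a rule, it covers the secondary outcomes, and no other rule in it would take the grade elsewhere.

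It can also be said that the linear-by-linear trend statistic is itself a 1-df chi-square, so the wording does not exclude it. True, but the unqualified term is normally read as Pearson's test.

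Stronger readings that a reader might infer, and that the documents do not support:

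- *The plan loses 15 to 20 points of power on the radiographic outcome.* That is one region of an assumed range. Nothing in the article fixes the grade distribution or the effect.
- *The shift will always be tested on 3 df, and the upper grades will be rare.* The article gives no expected frequencies. If the upper grades are rare, empty categories reduce the df.
- *The ordered test has no downside.* It has much less power against a non-monotone difference, although that is not the natural question for a severity grade.
- *The whole radiographic outcome, or the MEPI, is affected.* Ossification types are unordered, so chi-square is suitable in kind there. The article does not say that the MEPI will be tested in its four classes.
- *A difference would be missed only because of the test.* In the step 3 scenarios the ordered test itself has only 34 to 77% power.

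**Conclusion.** The point holds in a limited form. The stated rule sends an ordered 0 to 3 grade to a test that ignores its order, and in every consistent-shift scenario tried, the ordered test had more power while holding its size near 5%.

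The gain depends on what is assumed at 41 per arm under a proportional-odds shift: about 15 to 20 points for OR 2.5 to 3.5 with 25 to 50% of plaster patients showing any change, about 5 to 6 points at OR 1.5, and about 3 to 6 points (2 at OR 1.5) if about 95% are grade 0.

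Chi-square remains valid here and does not inflate false positives. The matter is efficiency for one component of a secondary outcome. The primary Quick-DASH comparison and the sample size do not depend on it.

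**What to change.** Add one sentence to the Statistical analysis section: ordered categorical outcomes, namely the degenerative grade, are compared with a tie-corrected Mann-Whitney test or a linear-by-linear trend test, in the exact version if counts are sparse. Name one of the two tests. Keep chi-square for unordered categories such as the type of heterotopic ossification.

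Fix this before the one-year radiographs are analysed, so that the test is not chosen after the data are seen. The cost is one sentence and standard software. The trade-off is lower power against a non-monotone difference. Tabulating the grade counts by arm would let a reader see such a pattern.
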